### Outcomes {12}

The primary outcome measure of this cRCT will be the number of first-time malaria infections (*Plasmodium falciparum* (Pf)) during the intervention period (24 months) as measured by microscopy in children aged between 6 months and 10 years.

Secondary outcome measures include:
2.Number of overall new *Plasmodium falciparum* malaria infections during the intervention period (24 months) as measured by microscopy in children aged between 6 months and 10 years;3.Number of first-time *Plasmodium falciparum* malaria infections during the intervention period (24 months) by two age groups (≤ 6–59 months old; 5–10 years old) as measured by microscopy in children aged between 6 months and 10 years;4.Number of overall *Plasmodium falciparum* malaria infections during the intervention period (24 months) by two age groups (≤ 6–59 months old; 5 years to 10 years old) as measured by microscopy in children aged between 6 months and 10 years;5.Anopheline-human contact (indoor and outdoor) using human biting rate (HBR) as an indicator for all anophelines and by anopheline species as measured by human landing catch (HLC) during 12-h intervals on a quarterly basis during the intervention period (24 months);6.Anopheline parity rate as an indicator of population age structure for all anophelines and by anopheline species as measured by mosquito ovarian dissections from a sub-sample of anophelines collected during HLC procedures during the intervention period (24 months);7.Anopheline infectivity using sporozoite rate as an indicator for all anophelines and by anopheline species as measured by laboratory detection of sporozoites in mosquito head-preps from a sub-sample of anophelines collected during HLC and/or CDC-light trap procedures during intervention period (24 months);8.Anopheline infectivity using entomological inoculation rate (EIR) during the intervention period (24 months) as an indicator for all anophelines and by anopheline species as measured by calculating the number of sporozoite-infected anopheline mosquitoes captured per person during intervention period from HLC and/or CDC-light trap procedures;9.CDC-light trap indoor density for all anophelines and by anopheline species as measured by CDC-light trap collections during 12-h intervals on a monthly basis during the intervention period (24 months);10.Insecticide resistance as measured by WHO filter paper test and CDC bottle assays during the baseline (6 months) and intervention period (24 months);11.Adverse events (AEs) and serious adverse events (SAEs) as measured by solicited and unsolicited reports during baseline (6 months) and intervention period (24 months). Mean, minimum and maximum frequency, and percentage of AEs and SAEs across clusters among enrolled subjects will be summarized by the treatment arm.

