#### Entomological collections

Twenty clusters (10 SR, 10 placebo) will be randomly selected to estimate the impact of the SR on entomological measures of malaria transmission. Within each cluster, light trap collections will be conducted monthly in 10 randomly selected HHs to assess the impact of SRs on the density of *Anopheles* mosquitoes indoors. The light traps will be deployed next to a person sleeping under a net and will run from approximately 6 pm to 6 am. The 10 SR and 10 placebo clusters will be randomly selected at the beginning of the study and will remain fixed throughout the study. HHs will be sampled with replacement and therefore will be eligible for repeated sampling throughout the study. HHs enrolled in the cohort study will not be eligible for mosquito sampling.

HLCs will be done indoors and outdoors in 6 intervention and 6 control clusters (the 12 clusters will remain fixed throughout the study) in four houses (randomly selected) in each cluster for the period of 2 nights (total of 48 houses across both arms) once every quarter (3 months) to determine the effect of SR on the host-seeking behavior of mosquitoes. The same clusters and the houses will be sampled each sampling period. SR and placebo clusters will be selected in pairs to reduce the degree of heterogeneity between two arms. Sentinel houses will be chosen so they are balanced as to house design and inhabitants to reduce bias due to mosquito density heterogeneity (i.e., some houses may be more attractive to mosquitoes than others). HHs with children enrolled in the cohort are not eligible for the HLCs. One pair of clusters will be sampled on any given night. Collections will start at 6 pm each night with one person inside and one person outside. The teams will collect for 45 min each hour and then take a 15-min break before starting the next hour of collection. At midnight, a new team will begin collecting and will continue until 6 am. Mosquitoes will be sorted by site, date, and time of collection. All mosquitoes will be identified to species and all female anopheline mosquitoes will be tested for the presence of sporozoites by ELISA and/or PCR. A subset of up to 30 per cluster per sampling period will be dissected for parity.

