##### Effects of SR on entomological endpoints

The endpoints in the entomological analysis will include the HBR (number of anopheline caught during the 12-hr interval overnight), anopheline parity rate, anopheline sporozoite rate, anopheline EIR, and the anopheline indoor density collected by light-trap.

We will report the frequencies and proportions of each mosquito Genus and species (anopheline and non-anophelines) collected using HLC and light trap methods across clusters and treatment arm.

The time profile plots of each aggregated entomological endpoint will be obtained over the baseline and intervention period. An appropriate statistical model for the HBR will be identified after examining the distributional characteristics of the HBR data, which are likely to follow (zero-inflated) Poisson distribution, or (zero-inflated) negative binomial distribution if there is over-dispersion. The covariates in the models will include the fixed effects of intervention, time, cluster population size, number of houses in a cluster, location (inside or outside), location and intervention interaction; and a random effect for cluster. The ratio between SR and placebo in HBR will be estimated. A similar model will be applied to analyze the density of mosquitoes caught by light traps. The ratio between SR and placebo on light trap density will be estimated.

The model for parity rate will be the (zero-inflated) Poisson distribution or a (zero-inflated) negative binomial distribution with the daily porous mosquitos as the outcome and the daily HBR as the offset, and the same set of covariates as those used in the model for analyzing HBR. The model for the sporozoite rate will be similar to the parity rate with the change of outcome variable to daily mosquitos with positive sporozoite. Note, if the data on parity and sporozoite positivity are highly unbalanced (not in terms of the distributions between the treatment arms, but the marginal distribution of the variable itself; e.g., 99% nulliparous or 99% negative sporozoite), then the model might lead to unstable estimates or the model might not even converge. In such cases, only summary statistics will be provided.

Summary statistics will be provided on EIR and the insecticide resistance at baseline and per year during the intervention period by treatment group.

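### Parity is modelled per mosquito caught but read only on a capped dissected sub-sample, so the SR/placebo parity ratio is biased upward wherever the cap binds and SR lowers the catch

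*Protocol article*

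**What the plan says.** In *Effects of SR on entomological endpoints*, the parity model is a (zero-inflated) Poisson or negative binomial regression "with the daily porous mosquitos as the outcome and the daily HBR as the offset" (*porous* is read here as parous). The same section defines the offset variable as "the HBR (number of anopheline caught during the 12-hr interval overnight", which is the total catch.

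The numerator is limited in two other places. *Entomological collections* states: "A subset of up to 30 per cluster per sampling period will be dissected for parity". *Outcomes {12}* lists parity as a secondary outcome "as measured by mosquito ovarian dissections from a sub-sample of anophelines collected during HLC procedures".

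For sporozoites the analysis section says: "The model for the sporozoite rate will be similar to the parity rate with the change of outcome variable to daily mosquitos with positive sporozoite". The protocol describes the testing in two ways. *Entomological collections* says "all female anopheline mosquitoes will be tested for the presence of sporozoites by ELISA and/or PCR", whereas *Outcomes {12}* speaks of "laboratory detection of sporozoites in mosquito head-preps from a sub-sample of anophelines collected during HLC and/or CDC-light trap procedures".

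**The concern.** A mosquito that is not dissected cannot be counted as parous. The outcome therefore comes from the dissected mosquitoes, while the offset counts every mosquito caught. The fitted rate is parous per caught, which equals parity times the fraction dissected.

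If that fraction were the same in both arms, it would cancel from the SR/placebo ratio. Under a fixed cap it need not be the same, because the fraction falls as the catch rises. HBR is itself an outcome that the repellent is meant to reduce. A lower catch in SR clusters then means a larger share dissected there, and this appears as higher parity. The listed covariates (time, cluster size, number of houses, location and its interaction with intervention) do not carry the fraction dissected and cannot remove the effect.

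Parity is a named secondary outcome, and *Secondary Objectives* lists it among the correlates meant to set benchmarks for later repellent trials. The bias runs opposite to the hoped-for reduction, so it can mask a true fall or report a rise that did not occur.

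**Working it through.** The protocol states no effect size, power or expected HBR for parity, so there is no planned figure to reproduce.

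**Inputs from the protocol** (*Entomological collections*): 4 houses per cluster, 2 nights per quarterly round, one collector indoors and one outdoors; 6 SR and 6 placebo clusters; at most 30 dissected per cluster and round.

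**Assumptions:** M, the placebo catch per cluster-quarter; r, the SR/placebo catch ratio; true parity p equal in both arms; dissection up to the cap; the offset entered as log(catch). The work is at cluster-quarter level.

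**Step 1: when the cap binds.** 4 × 2 × 2 = 16 person-nights per cluster-quarter. The cap binds above 30/16 = 1.875, about 1.9 anophelines per person-night.

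**Step 2: closed form.** Expected parous count = p × min(30, catch). Dividing by the catch and taking the SR/placebo ratio:

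apparent ratio = [min(30, rM)/(rM)] / [min(30, M)/M]

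The true ratio is 1. For r below 1 the expression lies between 1 and 1/r. It equals 1/r once both arms reach the cap: (30/(rM)) / (30/M) = 1/r.

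| M (per person-night) | r = 0.9 | r = 0.7 | r = 0.5 |
|---|---|---|---|
| 15 (0.94) | 1.00 | 1.00 | 1.00 |
| 30 (1.88) | 1.00 | 1.00 | 1.00 |
| 40 (2.50) | 1.11 | 1.33 | 1.33 |
| 60 (3.75) | 1.11 | 1.43 | 2.00 |
| 300 (18.75) | 1.11 | 1.43 | 2.00 |

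Example for M = 60, r = 0.7: the SR catch is 42 and the fraction dissected 30/42 = 0.714; in placebo it is 30/60 = 0.50; 0.714/0.50 = 1.43.

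**Step 3: masking.** The apparent ratio is the true ratio times this factor. With both arms above the cap and r = 0.7, a true parity ratio of 0.70 would read 0.70 × 1/0.70 = 1.00.

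**Step 4: simulation with variable catches.** 6 against 6 clusters, 8 quarters, negative binomial catch (size 2), cluster SD 0.3 on the log scale, parity 0.6 in both arms, Poisson regression with cluster-robust errors, 400 runs per setting. Apparent ratio with total catch as offset:

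| Mean placebo catch | r = 1.0 | r = 0.7 | r = 0.5 |
|---|---|---|---|
| 10 | 0.989 | 1.018 | 1.030 |
| 30 | 0.995 | 1.196 | 1.328 |
| 60 | 0.994 | 1.322 | 1.608 |
| 100 | 0.978 | 1.365 | 1.829 |
| 300 | 0.995 | 1.398 | 1.958 |

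Bias already appears at a mean of 30 because individual catches vary and some exceed the cap. With the number dissected as offset, the ratio is 0.995 to 1.004 in all 15 settings.

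At r = 0.5 and M of 60 or more, 80–85% of runs gave two-sided p < 0.05 with total catch as offset, against 7–10% with the number dissected. Even at r = 1 the total-catch model rejected in about 11–12% of runs, because cluster-robust errors are too small with 12 clusters. The argument rests on the point estimates.

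**Step 5: sporozoites.** The cap of 30 is stated for parity only. If all HLC females are tested and only HLC mosquitoes are counted, total HLC catch is a valid denominator. If a sub-sample is tested, or light-trap mosquitoes enter the numerator, HBR no longer matches it, since HBR does not count light-trap catches. The protocol supports both readings.

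**The case against.** The strongest reply is that the bias is conditional and its conditions are not quantified. The protocol gives no HBR, and the 30% and 50% catch reductions are assumptions; its own 30% is the malaria PE. Transmission has one peak (July to November) and HLC is quarterly, so some rounds may stay under the cap and dilute a pooled ratio. At a mean catch of 10 per cluster-quarter the distortion is only 2–3%. All of this stands. A reader might infer that parity will appear to rise in the SR arm. The documents support that only where the cap binds and the catch differs by arm, and 1.43 and 2.00 are ceilings.

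A reader might also extend the point to sporozoite rates because the model form is shared. That is not supported: *Entomological collections* says all female anophelines are tested. What remains is a conflict with *Outcomes {12}*, with no demonstrated bias.

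A third tempting inference is that the wrong rate feeds the analysis relating entomology to malaria hazard. That section handles parity in a similar fashion to HBR but does not say that the parity rate is parous/HBR; it could be parous/dissected. It is also exploratory and depends on sufficient data.

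Finally, the primary endpoint, the sample size and the overall-infection analysis are untouched, and the bias cannot create a false parity benefit. That limits the severity. It does not repair the parity model, because no passage rescales for the fraction dissected.

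**Conclusion.** The point holds for parity. As written, the numerator and the offset rest on different sets of mosquitoes, and the SR/placebo parity ratio is multiplied by a factor between 1 and 1/(catch ratio) whenever SR lowers the catch. The factor is 1 if every cluster-round yields 30 or fewer mosquitoes and all are dissected. It reaches 1.43 or 2.00 for assumed catch reductions of 30% or 50% when both arms are at the cap. The realised size depends on catch levels and catch ratio, neither of which the protocol gives. Sporozoite testing needs reconciling, but no bias is shown if all HLC females are tested and only those are counted. Severity: should-fix, because a secondary outcome and candidate correlate can be masked or reversed while the malaria analyses are unaffected.

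**What to change.** - **Parity model:** replace daily HBR by log(number dissected) as the offset, or fit a binomial model of parous out of dissected. Either removes the bias; keeping the stated count model with the new offset is enough. Cluster-nights with none dissected contribute no information.
- **Link to malaria hazard:** state that any parity rate used there is parous divided by dissected.
- **Sporozoites:** reconcile *Entomological collections* (all females tested) with *Outcomes {12}* (a sub-sample, HLC and/or light trap), and use the number tested, by collection method, as the denominator.

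The cost is a wording change, best made before unblinding. It needs only the counts dissected and tested, which the laboratory work produces. No sample size, visit or collection changes.

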##### Relationship between epidemiological and entomological endpoints for anopheline mosquitoes

To explore the relationship between the malaria hazard rate and the entomological endpoints, a similar model as the cloglog models used to address the primary objective on the first-time malaria infection and the secondary endpoint on the overall malaria infection will be applied to the epidemiological and entomological data in the clusters from which the entomological data are collected. The random effects and the individual-level and, HH-level covariates will the same as the cloglog models, and the cluster-level covariates will include the baseline incidence rate, cluster population size, and a covariate that captures the entomological information. Specifically, for HBR, the measurement to be paired with a malaria diagnosis in an individual is average daily HBR taken within 7 to 28 days before the diagnosis over the 2-week period and over the sentinel HHs where entomological endpoints are collected in the same cluster to which the individual belongs. The regression coefficient associated with log (HBR) quantifies the change in the malaria hazard rate on the log scale, given a one unit increase in log (HBR). For parity rate and sporozoite positivity rate, as long as there is enough data collected on these two endpoints and they are not highly unbalanced with regard to its marginal distribution (e.g., 99% mosquitos caught are nulliparous or sporozoite negative), the relationship between the malaria hazard rate and those two will also be investigated in a similar fashion as for HBR.

### Interim analyses {21b}

No interim analysis will be performed on the malaria and entomological data collected from the intervention period post randomization. The baseline data will be analyzed at the mid-point of the baseline period and at the completion of the baseline period to estimate the first-time and overall infection rates and their variability, and the mosquito density across the enrolled clustered.

### Methods for additional analyses (e.g. subgroup analyses) {20b}

#### Temporality of PE effects

It is expected that malaria incidence changes by seasonality (rainy vs dry) and year. To examine the temporality of malaria incidence rates and the PE effect, a supplementary analysis will be performed by adding the seasonality (Jun–Dec/wet/peak and Jan–May/dry/low) and year (1 and 2) and their interaction with intervention to the covariate list in the cloglog models used for analyzing the first-time and overall infections. The PE will be estimated by seasonality and year.

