### Trial design {8}

The study design is a cluster randomized control double-blinded clinical trial with 30 clusters per treatment arm (SR intervention and placebo), with a 6-month baseline follow-up period, and a post cluster randomization follow-up period of 24 months with intervention. For the evaluation of the primary objective, 26 subjects (HHs) are required within each cluster factoring in a 35% loss-to-follow-up (LTFU) rate. It is expected that 80% of the baseline subjects (HHs) will continue to participate in the intervention period therefore a total of 32 subjects (HHs) will be enrolled at the start of baseline. At least one child aged from ≥ 6 months to < 10 years of age from each HH will be recruited for malaria follow-up during each baseline and intervention trial periods.

Twenty clusters (10 SR, 10 placebo) will be randomly selected to estimate the impact of the SR intervention on entomological measures of malaria transmission using CDC light traps. From these 20 clusters, a subset of 12 clusters (6 SR, 6 placebo) will be randomly selected for HLC. Light trap collections will be conducted in 10 randomly selected houses every month to assess the impact of the SR intervention on the indoor density of *Anopheles* mosquitoes. Indoor HLC will be conducted in four randomly selected houses within each of the subset 12 clusters every quarter. Four houses will be randomly selected at the start baseline, for a total of 48 sentinel houses). These 48 houses will remain fixed throughout the trial period.

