#### Primary hypothesis on first-time malaria infection

The sample size determination on the required number of subjects (HHs) per cluster for testing the primary hypothesis on PE is based on the hazard rate comparison in the proportional hazards regression model [7, 8]. With the following specifications: 1-sided type-I error rate = 5% (because the primary hypothesis is one-sided as SR is very unlikely to increase the hazard rate of malaria infection compared to placebo), true PE = 30%, a between-cluster coefficient of variance (CV) of hazard rate = 47% (based on the historical data collected from Mali) then 788 independent first-time malaria events will need to be observed to reach 80% power in testing the primary hypothesis on PE.

With a baseline first-time malaria infection hazard rate of 1.0 per person-year (ppy), 30 clusters per treatment, 26 subjects (HHs) per cluster (factoring in a LTFU rate at 35%) in each treatment arm post randomization are expected to yield 788 independent first-time malaria events within 24 months follow-up period per cohort post randomization to yield 80% power. If, by the end of the 2-year study, 788 independent malaria events are not reached, the study may extend until 788 events are collected without inflating the type I error rate in the testing of the primary hypothesis. The same number of HHs (26) will be recruited into the baseline period. It is expected that 80% of the baseline HHs will continue to participate in the intervention period.

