#### Statistical methods—primary endpoint (ITT population)

The baseline characteristics of the enrolled subjects, HHs, and clusters will be summarized by treatment arm. Specifically, we will examine subject age and gender at the individual level, wall type and roof type, floor height, house open eaves, # of window, # of doors at the HH levels, and cluster population and baseline overall infection incidence at the cluster level.

The primary hypothesis on PE against the first-time malaria infection will be tested by comparing the hazard rates of first-time malaria infection between SR and placebo upon the completion of the study in the ITT population via a cloglog regression for the interval-censored time to event data. The model will include the treatment arm (SR vs. placebo), relevant baseline covariates, and a random effect that accounts for the dependency among data collected from the same cluster. PE against the first-time infection is estimated by ($$ 1-\exp\ \left(\hat{\beta}\right)\ \Big)\times $$100%, where$$ \hat{\beta} $$ is the estimated regression coefficient associated with the treatment group, with a 90% 2-sided confidence Interval (CI) based on the Wald test. The lower bound of the 90% CI corresponds to the lower bound of the 95% 1-sided CI (the hypothesis is one-sided).

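### Season- and year-specific PE: the models omit village-by-season and village-by-year variation, so intervals for differences in PE between periods can be too narrow (supplementary analysis, minor)

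*Protocol article*

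**What the plan says.** The section on temporality of PE effects (Methods for additional analyses {20b}) describes a supplementary analysis. Season (June–December against January–May), year (1 and 2) and "their interaction with intervention to the covariate list in the cloglog models used for analyzing the first-time and overall infections" are added. The stated output is: "The PE will be estimated by seasonality and year".

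The models being extended are defined earlier. For first-time infection the cloglog model has treatment, baseline covariates and "a random effect that accounts for the dependency among data collected from the same cluster", with a 90% Wald interval (Statistical methods—primary endpoint). For overall infection one more random effect, for the individual child, is added (Statistical methods—secondary endpoints). Neither section states a cluster-by-time term or a robust variance, and the temporality section leaves the random part alone.

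The design has "30 clusters per treatment arm (SR intervention and placebo"), and villages are the unit of randomization. The only figure on between-village variation is one overall value: "a between-cluster coefficient of variance (CV) of hazard rate = 47" per cent (Sample size {14}).

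**The concern.** A treatment-by-season or treatment-by-year effect asks whether the change in infection rate from one period to the next differs between arms. Each village contributes its own change, and the arms are compared over 30 and 30 villages. A village intercept raises or lowers both periods equally, so it drops out of the change. If one village has a sharper wet season than another, or a worse second year, that difference has nowhere to go in the model: the cluster effect is constant over time, the child effect is also constant over time, and a cloglog model for binary data has no dispersion parameter. The standard error of the difference in PE then reflects little more than event counts.

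At stake is any statement that protection differs between wet and dry seasons or changes in year 2. The findings go to the WHO Vector Control Advisory Group, and readers would use such statements in judging how the product performs over time.

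**Working it through.** **Inputs from the article.** 30 villages per arm; 26 children per village with 35% loss to follow-up; 24 months; PE 30%; "baseline first-time malaria infection hazard rate of 1.0 per person-year (ppy"); CV 47%; "1-sided type-I error rate = 5" per cent; 80% power.

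**Inputs that are assumed.** The share s of between-village log-rate variance that is specific to a season or year (0 to 50%); a wet:dry hazard ratio of 4 (2 and 8 also run); an overall infection rate of 1 or 2 per person-year. The article gives none of these.

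**Reproducing the plan's own figure.** The article says "788 independent first-time malaria events will need to be observed to reach 80% power". The Hayes–Bennett person-years formula without the extra cluster is

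c = (z₀.₉₅ + z₀.₈₀)² × [(λ₀+λ₁)/y + k²(λ₀²+λ₁²)] / (λ₀−λ₁)².

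With c = 30, λ₀ = 1.0, λ₁ = 0.7, k = 0.47:
- 30 × 0.09 / 6.183 = 0.4367
- k²(λ₀²+λ₁²) = 0.2209 × 1.49 = 0.3291
- y = 1.7 / (0.4367 − 0.3291) = 15.8 person-years per village
- events = 30 × 15.8 × 1.7 = 806, within 3% of 788; power at 788 events is 79.8%.

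So the single CV of 47% is the between-village variation the sample size rests on. It is not split by period.

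**Hand check of the contrast (overall infection, 1 per person-year).** Between-village log-rate variance is ln(1 + 0.47²) = 0.1996. The simulations below give about 2,020 events, hence about 1,188 placebo (2,020/1.7) and 832 SR.
- Variance the model sees, year contrast, events split evenly over years: 4/1,188 + 4/832 = 0.00818.
- Season contrast: the wet share of events is 7×4/(7×4+5) = 28/33, so 1/1,008 + 1/180 + 1/706 + 1/126 = 0.0159.
- Variance it omits: 2 arms × 2 periods × s × 0.1996/30. This is 0.00665 at s = 25% and 0.0133 at s = 50%.
- True rejection rate at nominal 5%: 2[1 − Φ(1.96/√(1 + omitted/seen))].
- Year: 14.6% (s = 25%) and 22.7% (s = 50%). Season: 10.0% and 14.8%.

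**Simulation.** 60 villages × 26 children × 24 monthly visits, 35% dropout, PE 30% in every period (so no true difference), total CV 47%. Each data set was fitted by a cloglog model with one village random intercept and both interactions, using Wald tests. There were 1,000 runs for most scenarios and 500 for those at 2 per person-year with s above 0 (Monte Carlo SE about 0.7 and 1.0 points at 5%). Rejection at nominal two-sided 5%, wet:dry ratio 4, season / year:

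| Period-specific share s | First-time infection | Overall, 1 per person-year | Overall, 2 per person-year |
|---|---|---|---|
| 0 | 5.2% / 3.6% | 4.7% / 5.2% | 5.0% / 4.8% |
| 5% each | 6.2% / 5.4% | 6.1% / 7.3% | 7.2% / 9.0% |
| 10% each | 6.9% / 6.1% | 6.9% / 9.4% | not run at ratio 4 |
| 25% each | 8.2% / 8.2% | 10.2% / 14.6% | 16.2% / 19.4% |
| 50% on that factor alone | 11.3% / 13.9% | 15.9% / 21.9% | 24.6% / 31.6% |

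The hand check agrees closely with the third column. With a wet:dry ratio of 2 or 8 and s of 10–25%, first-time infection gives 4.9–8.9% and overall infection 5.7–23.4%.

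**The quantity the article promises.** A period-specific PE is itself a between-village comparison, so the village variance does enter its standard error. In a Poisson random-intercept simulation (400 runs per scenario, Monte Carlo SE about 1.5 points), nominal 90% intervals for period-specific PE missed the truth 12–13% of the time at s = 0, 8–16% at s = 20% and 14–18% at s = 50%. In the same runs at s = 50%, the interval for the difference missed 27% (season) and 33% (year).

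**After the change.** With a cluster-robust variance and t on 58 df, rejection was 4.2–5.8% in all five scenarios run. A t-test on village log-rate changes held about 4–6% for overall infection.

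**The case against.** Several points count against a strong reading.

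- A reader might infer that interaction tests will reject two to five times too often. The article does not support that. It gives no correlation of village rates over time, and inflation is nil if villages keep their relative levels. For first-time infection, the primary endpoint, the error is about 1.1 to 1.8 times nominal up to a 25% share and 2 to 3 times only at 50%. All villages lie in one district with one transmission peak, which gives no reason to prefer a low correlation over a high one. This stands.
- The temporality section names no interaction test, threshold or decision rule. It promises PE by season and year, and those intervals are only mildly affected. This stands. It is therefore also too much to say that chance village changes will be reported as waning. Still, estimates shown side by side from an interaction model invite comparison, and the comparison is where the error sits.
- A reader might infer that infections within a village-season are treated as independent. They are not: the village effect stays in, and the overall model also has a child effect. What is missing is only variation in village rates over time.
- The random structure could be left to the analysis plan, and an intercept is an interpretation of the article's single random effect. This stands only in part. The article does fix the models and says what is added to them, and its wording is most naturally read as an intercept.
- The analysis is supplementary. This stands and sets the severity.

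**Conclusion.** The point holds in conditional form and is minor. As written, the season and year analyses have no term for village rates that shift differently between periods. If such shifts exist, standard errors for differences in PE between seasons or years are too small, and intervals for the period-specific PEs are somewhat too narrow.

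The error at nominal 5% for the difference ranges from about nominal to about 8% (25% share) and 11–14% (50% share) for first-time infection. For overall infection at 1 per person-year it is about 10–15% and 16–22%, and higher at higher incidence. These figures rest on assumed shares and wet:dry ratios, and on simulations without extra child-level frailty. Which row of the table applies cannot be settled from the article.

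Nothing here touches the main tests of PE against first-time or overall infection, or the sample size.

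**What to change.** In the temporality section, state that the interaction models also carry a village-by-season and a village-by-year random effect (random slopes of season and year by village). Alternatively, keep the model and use a cluster-robust variance with t on 58 df (60 villages minus 2 arms), or compare village log-rate changes between arms. Base both the period-specific PE intervals and the intervals for their differences on the chosen method.

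The robust and cluster-level versions are the ones checked above; the random-slope version addresses the same omission but was not simulated. The cluster-level version suits overall infection better, because a village with no first infection in a period has no log rate.

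The cost is a sentence in the plan, one more variance term per model if random slopes are used, and somewhat wider intervals. No new data are needed.
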